## Abstract

The optimal airway management strategy during cardiopulmonary resuscitation is uncertain. In the case of out-of-hospital cardiac arrest, a high chest compression fraction is paramount to obtain the return of spontaneous circulation and improve survival and neurological outcomes. To improve this fraction, providing continuous chest compressions should be more effective than using the conventional 30:2 ratio. Airway management should, however, be adapted, since face-mask ventilation can hardly be carried out while continuous compressions are administered. The early insertion of a supraglottic device could therefore improve the chest compression fraction by allowing ventilation while maintaining compressions. This is a protocol for a multicenter, parallel, randomized simulation study. Depending on randomization, each team made up of paramedics and emergency medical technicians will manage the 10-min scenario according either to the standard approach (30 compressions with two face-mask ventilations) or to the experimental approach (continuous manual compressions with early insertion of an i-gel^®^ supraglottic device to deliver asynchronous ventilations). The primary outcome will be the chest compression fraction during the first two minutes of cardiopulmonary resuscitation. Secondary outcomes will be chest compression fraction (per cycle and overall), compressions and ventilations quality, time to first shock and to first ventilation, user satisfaction, and providers’ self-assessed cognitive load.

## 1. Introduction

### 1.1. Background

Achieving high-quality cardiopulmonary resuscitation (CPR) requires the provision of chest compressions of adequate depth and rate while avoiding interruptions [1]. The chest compression fraction (CCF) is the proportion of time spent performing compressions, and can be increased by minimizing interruptions. The latest European Resuscitation Council (ERC) recommendations emphasize the importance of applying the highest possible quality of chest compressions with minimal interruption [2], and the American Heart Association (AHA) recommendations state that the CCF should be equal to at least 60%, and ideally exceed 80% [1]. In animal studies, continuous compressions are associated with a higher rate of good neurological outcomes compared to a 30:2 regimen [3,4]. Human clinical trials have shown that maintaining a high CCF is linked to a higher rate of return of spontaneous circulation (ROSC), survival, and favourable neurological outcomes both in shockable and non-shockable rhythms [5,6,7,8,9,10,11]. For instance, Christenson et al. found that a 10% increase in CCF is approximately equal to an 11% increase in survival [8].

The optimal airway management strategy during CPR and after ROSC is uncertain [12,13,14,15]. Endotracheal intubation (ETI) remains the most effective and safest technique, but requires great skill that must be maintained by regular practice to be efficient and avoid complications [16,17,18]. The use of supraglottic airway (SGA) devices during CPR is associated with a lower incidence of regurgitation when compared to face mask ventilation (FMV) [19]. The i-gel^®^ is an effective SGA device that can be rapidly inserted with high success rates [20,21,22,23,24,25,26,27,28,29]. Most of the time, the i-gel^®^, which has a thermoplastic non-inflatable cuff, enables the delivery of continuous chest compressions with providers reporting no leak in the vast majority of patients [30]. This device also confers relative airway protection, as aspiration is less frequent compared to FMV [31]. In the AIRWAYS-2 trial, regurgitation and aspiration rates were not significantly different between the ETI and SGA groups [32].

In addition, the use of SGA enables the adjunction of end-tidal CO_2_ to monitor the quality of CPR and its optimization, which could also be useful to help for ROSC detection [1].

The hypothesis is that the experimental approach could improve CCF during out-of-hospital cardiac arrest (OHCA), with a reasonable time of about 60 s to first effective ventilation.

### 1.2. Objectives

The primary aim of this study is to determine whether the immediate insertion of an i-gel^®^ while providing continuous chest compressions followed by asynchronous ventilations can increase the CCF compared to the 30 compressions/two ventilations standard approach in a simulated model of OHCA after a short teaching intervention.

The secondary objective is to compare the basic life-support (BLS) quality by assessing the chest compressions and ventilations parameters using the International Liaison Committee on Resuscitation (ILCOR), ERC and AHA up-to-date recommendations [1,33,34].

## 2. Materials and Methods

### 2.1. Study Design

This will be a multicenter, parallel, randomized, superiority simulation study. This protocol was designed in accordance with the Standard Protocol Items: Recommendations for Interventional Trials (SPIRIT) statement (SPIRIT Checklist as Supplementary Table S1) [35]. The Consolidated Standards of Reporting Trials (CONSORT) flow chart of the trial is displayed in Figure 1 and the SPIRIT Figure describing the timeline is displayed in Table 1, as recommended [35,36]. 

### 2.2. Setting

In Switzerland, all paramedics graduate from Colleges of Higher Education in Ambulance Care after a 3-year (5400 h) training curriculum covering most aspects of prehospital emergency care. Paramedics are trained to treat most of the prehospital emergencies autonomously and can administer several advanced life-support (ALS) treatments by virtue of emergency care protocols elaborated by prehospital medical directors. Emergency medical technicians (EMTs) graduate after a 1-year curriculum focusing on BLS aspects and are able to assist paramedics in taking care of critically ill patients; they can also care for patients with non-life-threatening conditions under direct supervision by a paramedic. 

Due to the Swiss federal system and owing to the individual design of treatment protocols by different medical directors, there is substantial inter-cantonal heterogeneity among Swiss Emergency Medical Services (EMS) and more largely between the healthcare systems in this country. However, the three-tiered response to OHCA is largely similar. The first tier is made of a system of lay or professional first-responders [37], who are registered volunteers dispatched by the emergency medical communication center (EMMC) to perform BLS manoeuvres when OHCA is identified on the call. Simultaneously, the second tier, which is composed of an ALS ambulance staffed either by an EMT and a paramedic or by two paramedics, is also dispatched. The third tier, which consists of a medical reinforcement, is available in most cantonal systems [38].

### 2.3. Trial Centers

The i-gel^®^ device has been largely used in Geneva for years, but some regions, such as Vaud and Valais, have not yet adopted its use widely. Therefore, this study will be performed in four different EMS from the cantons of Vaud and Valais in the French-speaking part of Switzerland. The study centers were the following: *Ambulance Riviera, Association Sécurité Riviera*, La Tour-de-Peilz, Vaud; *Compagnie d’Ambulances de l’Hôpital du Valais*, Martigny, Valais; *Service de Protection et de Sauvetage Lausanne*, Lausanne, Vaud *and Société de Transport en Ambulance Régionale, STAR Ambulances*, Épalinges, Vaud. All these services do not currently use the i-gel^®^ device in the field. They are applying the standard 30:2 approach. 

### 2.4. Participants, Study Flow and Recruitment

All registered paramedics and EMTs actively working in any of the participating study centers will be eligible for inclusion in the study. The exclusion criteria will be the following: member of study investigators, not to have undergone the 20 min workshop, or not to have followed the self-training session supported by the demonstration video. Participants will be recruited by the local study coordinator with the same email template (Supplementary File S2). Participants will be told the study is about OHCA management, but will not be informed of the outcomes studied. 

### 2.5. Study Sequence

The study sequence is displayed in Figure 2.

#### 2.5.1. Randomization

We will use two levels of randomization. Teams will be generated using an online balanced team generator [39]. For each trial center, a stratification by professional status will be made in order to be representative of the current practice in the field with at least one paramedic per team. In teams made up of an EMT and a paramedic, the paramedic will always be the “team leader”. In teams made up of two paramedics, they will choose their role, as in actual clinical practice.

The teams will then be randomized in one of the two study arms by opening an opaque, sealed envelope containing the approach to apply (standard or experimental) created using a stratified randomization list generated online by [name] ([name]) using a 1:1 ratio [40]. The actual standard 30:2 approach may be slightly different between the EMSs, for instance regarding service-specific task distribution, quality processes, prior specific training or local procedures during CPR. To take into account such discrepancies, a randomization stratified by service will be used.

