### 2.9. Sample Size Calculation, Data Extraction and Statistical Analysis

The sample size is based on an estimate as there are few relevant data available to compute it for such a study. The mean time required to deliver two ventilations is estimated to be around 4 s; two ventilations should be provided 5 times during the first cycle, therefore amounting to a total of 20 s of no-flow. In addition, the initial rhythm analysis should take about 8 s. Pooled together, these no-flow times should amount to 28 s out of the first 120 s cycle, therefore representing 23% of no-flow. The CCF should therefore be around 77% in the control group. In the experimental group, taking into account the time for rhythm analysis and shock, estimated to be around 8 s (same time as control group), the corresponding no-flow time should be about 7%, with a CCF of 93%. Based on observational data from case reviews and pilot tests, the variability of the data is estimated with a standard deviation of 12.

Twenty-four teams will be required in order to have a 90% chance of detecting, at the 5% significance level, an increase in the primary outcome measure from 77 in the control group to 93 in the experimental group.

The data extraction process will take place as follows: the CPREvents.xml file will be obtained by unzipping the SSX file proposed by Laerdal after each simulation with the SimMan manikin and saved in a comma-separated values (CSV) file. Then, this file will be uploaded in an SQL table (by phpMyAdmin, https://www.phpmyadmin.net/, V. 5.0.4, accessed on 23 February 2021). The variables of interest will be automatically generated in an accurate, reliable and reproducible manner using a PHP script specifically designed for the study (Supplementary File S7), from which a new CSV file will be extracted and imported directly into the statistics software. To minimize copying or typing errors, all data collected on paper CRF will be entered in duplicate using EpiData [52]. The consistency of the answers will then be checked by merging the two files in a common variable where discrepancies are listed. After resolving the discrepancies, data will be exported in a Stata DTA file. These two Stata databases will then be concatenated. Missing data will be treated as such. No imputation technique will be used.

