All data that could allow the data analyst to identify the group allocation will be deleted (e.g., number of insertion attempts). The groups will be renamed otherwise (groups “Teysachaux” and “Moléson”) and the curated database will be sent in Stata DTA file format to DT for formal analysis. All investigators will be able to access the curated and coded data set.

Distribution normality will be checked graphically for continuous variables, and the Shapiro–Wilk test will be used in case of doubt. If this assumption is checked, a Student’s t-test will be used to compare both groups; if not, the Mann–Whitney U test will be used. These variables will be described using mean (SD) or median (Q1; Q3) depending on their distribution. We will test proportions using Fisher’s exact test. They will be reported with their 95% confidence interval.

User satisfaction will be assessed graphically, then dichotomized into “Satisfied” versus “Not satisfied” before being tested using Fisher’s exact test. The cognitive load variable will be treated as continuous.

A two-sided p-value of 0.05 will be considered significant. All the statistical analyses will be performed using Stata V15.1 (StataCorp. 2017. Stata Statistical Software: Release 15. College Station, TX: StataCorp LLC).

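### The primary comparison omits the service factor used to stratify allocation; if services differ, the planned test is mildly conservative and loses some precision (minor)

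*Protocol article*

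**What the plan says.** Section 2.3 of the protocol article: "this study will be performed in four different EMS".

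Section 2.5.1 allocates teams "using a 1:1 ratio". It explains that the 30:2 approach may differ slightly from one service to another, through task distribution, quality processes, training or local procedures, and concludes: "To take into account such discrepancies, a randomization stratified by service will be used".

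Section 2.9 fixes the comparison for continuous variables, which include the primary outcome. If normality holds, "a Student’s t-test will be used to compare both groups; if not, the Mann–Whitney U test will be used". The significance rule is: "A two-sided p-value of 0.05 will be considered significant". No service term, stratified test or adjusted analysis is named anywhere. The sample size calculation in the same section is also a plain two-group one.

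**The concern.** Stratified allocation balances the arms within each service, so differences between services largely cancel out of the arm difference. A pooled two-group test does not use this. It still counts between-service variation as noise, so its standard error is larger than the true variability of the estimate. The test then rejects less often than its nominal 5% under the null, and the estimate is reported as less precise than it is.

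The article does not leave the method open: it names a test, and that test leaves out the factor that the design was built around. At stake is efficiency in a trial of 24 teams, not protection against a false positive.

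**Working it through.** **Inputs from the article**
- Effect: "an increase in the primary outcome measure from 77 in the control group to 93 in the experimental group", a difference of 16 points (section 2.9).
- Spread: "the variability of the data is estimated with a standard deviation of 12", one overall value not split into between- and within-service parts (section 2.9).
- Size: "Twenty-four teams will be required in order to have a 90% chance of detecting, at the 5% significance level" (section 2.9).
- Four services (section 2.3), 1:1 allocation stratified by service (section 2.5.1).

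**Assumptions, not in the article**
- Six teams per service, three per arm.
- A share ρ of the total variance 12² = 144 lies between services. ρ is not given, so a range is shown.
- The service effect is the same in both arms, except in the control-arm-only case under the objection.

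**1. Reproduce the plan's figure.** n per arm = 2(1.960 + 1.282)² × 12²/16² ≈ 2 × 10.51 × 0.5625 = 11.8, so 12 per arm and 24 teams. The normal approximation gives power 0.904. The exact t-test gives 0.877, which is the right baseline for the table below when ρ = 0.

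**2. Why the unadjusted standard error is too large.** With 3:3 in each service, the true variance of the arm difference is 2 × 144(1 − ρ)/12 = 24(1 − ρ). Within an arm of 12 teams (11 df), the expected sum of squares is 11(1 − ρ) × 144 from within services plus 3 × 3ρ × 144 from between them. The expected pooled variance is therefore 144(1 − 2ρ/11), and the t-test works with a squared standard error of about 24(1 − 2ρ/11).

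| ρ | true SE, √[24(1 − ρ)] | t-test SE, √[24(1 − 2ρ/11)] | ratio |
|---|---|---|---|
| 0 | 4.90 | 4.90 | 1.00 |
| 0.1 | 4.65 | 4.85 | 1.04 |
| 0.2 | 4.38 | 4.81 | 1.10 |
| 0.3 | 4.10 | 4.76 | 1.16 |

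**3. What this does to the test.** Simulated trials, total SD fixed at 12. The planned t-test (22 df) is compared with a linear model of arm plus service (24 − 4 − 1 = 19 df).

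| ρ | type I error, t-test | type I error, adjusted | power, t-test | power, adjusted | mean 95% CI width, t-test / adjusted |
|---|---|---|---|---|---|
| 0 | 5.0% | 5.0% | 87.5% | 87.0% | 20.1 / 20.3 |
| 0.05 | 4.6% | 5.0% | 88.4% | 88.8% | 20.0 / 19.7 |
| 0.1 | 4.2% | about 5% | 89.0% | 90.2% | 19.9 / 19.2 |
| 0.2 | 3.4% | about 5% | 90.3% | 93.1% | 19.7 / 18.1 |
| 0.3 | 2.9% | about 5% | 92.0% | 95.8% | 19.5 / 17.0 |

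Separate runs agreed to within about half a percentage point. The t-test's own power rises with ρ because the total SD is held at 12, so the variance left within services shrinks.

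**4. Variants.** The Mann–Whitney fallback shows the same pattern: type I error 4.5%, 3.6% and 2.3% at ρ = 0, 0.1 and 0.3. Unequal services (4, 4, 6 and 10 teams) give nearly the same results as equal ones.

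**The case against.** **The size is unknown.** The article gives no between-service variance and describes the differences as possible and slight. This stands: the table is a range under an assumption, and below about ρ = 0.05 nothing of practical importance is lost.

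**The stated reason concerns the control arm.** It is the standard approach that may vary; the experimental one is newly taught from one common procedure (sections 2.5.2 and 2.5.5). This stands too. With service effects confined to the control arm, the power of the two analyses differs by at most 0.6 points either way for ρ from 0.1 to 0.3. The t-test is still conservative, but less so (4.4% to 4.7% at ρ = 0.1, 3.6% to 3.7% at 0.3), and an additive service term recovers only part of that.

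**Balance within services is assumed.** The article gives no block size, and the team leader picks an envelope from a stack (section 2.5.4). Under effectively simple randomization the t-test has about 5% type I error. Adjustment then gains power at ρ = 0.3 (0.883 to 0.916) but loses it at ρ = 0.1 (0.869 to 0.840). Near-balance is what stratification is meant to deliver, so this limits the point without removing it.

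**A stronger reading is tempting.** A reader might infer that the planned p-value is invalid, that the true type I error is definitely below 5%, or that the trial is underpowered for this reason. The article does not support this. The error is conservative, so it cannot create a false positive. It arises only if services differ, and at ρ = 0.2 and 0.3 the unadjusted power is still above 90%. Nor does section 2.9 clearly promise a confidence interval for the CCF difference, so the widths above describe precision and do not show a defect in a stated interval.

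**Conclusion.** The point holds as a minor one. The design stratifies by service and the named primary test ignores service. If services shift both arms alike and allocation is balanced within them, the planned t-test gives up about 1.2, 2.8 and 3.8 points of power at ρ = 0.1, 0.2 and 0.3 (90.2 − 89.0, 93.1 − 90.3, 95.8 − 92.0), and its type I error falls to about 4.2%, 3.4% and 2.9%. If services do not differ, the planned test is slightly the better one. The 24 teams need not change on this account, and a significant result from the planned test would stand.

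**What to change.** In section 2.9, name as the primary analysis a linear regression of CCF on arm plus service (fixed effects), reporting the adjusted mean difference with its 95% CI. If normality is doubtful, use a permutation test of the same arm effect, permuting arms within service. With three teams per arm in each of four services there are 20⁴ = 160,000 such allocations, enough for an exact p-value.

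A service-stratified rank test (van Elteren) is the obvious alternative but does not suit strata this small. Its normal-approximation p-value has a true size of about 6.1% to 6.6%. Its exact version has a size of about 3.6% and power of 76.6% to 89.7%, below the planned t-test.

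Treat the team-level continuous secondary outcomes in the same way. Keep a service code in the curated dataset sent to the analyst. Both arms occur in every service, so the code does not reveal allocation.

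Cost: a sentence or two, no new data, and three degrees of freedom. With balanced allocation that is about half a power point if services do not differ. If the arms turn out badly unbalanced within services, the cost can reach about 3 points at ρ = 0.1.

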#### 2.5.2. Pre-Scenario Standardized Workshop

As an introduction, information about the study will be given and participants’ questions will be answered. Written consent will be obtained by [name] and the demographics data questionnaire will be individually completed. 

Then, the use of the i-gel^®^ device use will be taught by one of the investigators ([name]) in accordance with Peyton’s approach [41,42], because this approach has shown superiority [43], and is based on a standard operating procedure (Supplementary Files S3 and S4) created by study investigators following the manufacturer’s instructions:

(1) The instructor performs a complete insertion sequence in real-time without any comments;

(2) The instructor performs an insertion sequence with step-by-step explanations (description of key points);

(3) The learners guide the instructor step by step to perform the insertion;

(4) The learners do the complete insertion sequence then feedback could be given. They will perform this step a maximum of 3 times.

This workshop will last 20 min.

#### 2.5.3. Self-Managed Training Session

After the workshop, each team will have 20 min to self-train the introduction of the device into the complete OHCA management sequence on a CPR manikin permitting airway management. They will be supported by a demonstration video (https://www.youtube.com/watch?reload=9&v=UuX2cik_aBg, accessed on 23 February 2021), which they can use freely.

#### 2.5.4. Resuscitation Scenario

When entering the study room, an overview of the characteristics of the simulation manikin and of the use of the defibrillator will be given through a standardized video (https://www.youtube.com/watch?v=ifUj8xFSfy0, accessed on 23 February 2021). The team will then be asked to perform a 10 min highly realistic adult CPR scenario on a high-fidelity WiFi manikin. The procedure will be standardized across all sites to ensure that each participant is exposed to exactly the same scenario, with similar challenges in decision-making and treatment provided on the same manikin. The uniform delivery of the scenario will minimize confounders. The room will be exclusively devoted to the simulation to prevent unexpected interruptions or external stimuli. Participants will be told that the resuscitation scenario will be stopped after 10 min, independently of their actions, and that no feedback will be given. The simulation will be carried out without external pressure (witnesses, relatives, road traffic sounds, etc.).

The scenario will start with a clinical statement to recognize the life-threatening condition of the patient, given by one of the investigators as follows: *«Here is Michael, a 50-year-old man who suddenly collapsed 10 min ago. He is now unconscious, pale and seems not to be breathing. The medical reinforcement is already underway and will be on site in about ten minutes. No first responder has been dispatched by the EMMC, and no bystander is on scene».* The team leader will be asked to reformulate this statement (closed-loop communication) to ensure comprehension. He will then choose and open one of the envelopes of the stack. The opaque, sealed envelope will contain the approach they will have to apply: current practice approach or experimental approach. From this point on, there will be no more contact between the participants and the study team, except to stop the scenario.

The simulated patient will be apneic and pulse will be absent if checked. The first compression will be defined as T0. After placement of the pads, the defibrillator’s display will show ventricular fibrillation (VF). To increase simulation’s fidelity CPR waves will be automatically displayed when compressions are delivered. All subsequent rhythm analyses will show refractory VF, regardless of whether a shock is delivered. Participants will be able to obtain an intravenous access on first attempt. They should administer first 1 mg of epinephrine (at the earliest after the second shock), then a first-dose of amiodarone or lidocaine following local protocols (in accordance with the 2020 AHA adult cardiac arrest algorithm) [44]. The scenario will be stopped exactly 10 min after the first compression. There will be no further intervention or educational adjunct after the study period.

